# A feasibility study of a WhatsApp-delivered Transtheoretical Model-based intervention to promote healthy eating habits for firefighters in Hong Kong: a cluster randomized controlled trial

**DOI:** 10.1186/s13063-020-04258-6

**Published:** 2020-06-12

**Keywords:** Healthy eating habits, Health promotion, Body mass index, Fruit and vegetable consumption

## Abstract

**Background:**

Firefighters’ health is often affected by a high prevalence of obesity and cardiovascular diseases, which are common risk factors for sudden cardiac death. The aim of this study is to investigate the feasibility of enhancing healthy eating habits in firefighters through an education programme.

**Methods:**

This will be a cluster randomized control trial study. The participants will be assigned randomly into either control (health promotion pamphlet) or intervention (health promotion pamphlet and education materials through WhatsApp) groups. Changes in healthy eating habits will be assessed by a self-administered questionnaire and anthropometric measurements at three different time points.

**Discussion:**

More education is required in order to improve firefighters’ eating habits.

**Trial registration:**

ISRCTN registry identifier: Registered on 8 April 2019 ISRCTN95472464.

## Background

Obesity and being overweight have many adverse effects on the health of the population in general. Worldwide, in 2012, around 17.6 million people lost their lives due to cardiovascular diseases (CVDs) [1, 2]. Obesity or being overweight is a key factor that can increase the risk of CVDs [3, 4]. A high number of firefighters in the USA, UK and Hong Kong [5–7] have been identified as overweight or obese. Numerous studies have investigated obesity-related CVD risk factors in firefighters, and the results have illustrated this group to be particularly prone to fatal cardiac events [6, 8–12] compared to other professional groups. And yet, the fact is that firefighters need to be in good physical condition, as their work is hazardous. In the USA, approximately 45% of on-duty deaths are caused by sudden cardiac death (SCD) [13–15], with 90% of these events related to coronary heart disease (CHD) [6, 11]. No data have been found to identify any relationship between CVD and obesity in Hong Kong firefighters; however, about 40% have been classified as overweight or obese [16]. Therefore, this issue should be considered seriously.

One study identified that, with nearly 75% of all deaths in the general population globally attributed to CVDs, the major cause was unhealthy eating, such as inadequate intake of fruit and vegetables [17]. This phenomenon is worsening across the world. The long working hours and shift work have an impact on the amount of fruit and vegetables firefighters eat [18]. Their working conditions are unique, as they have 24-h work shifts, are in a quasi-military working organization and the pattern of generally routine firehouse-based activities is interrupted by unpredictable calls for emergency care [19]. Furthermore, firefighters are inclined to eat quickly while on duty, and sometimes their meals are interrupted by fire emergencies. All of these factors can combine to cause them to consume inadequate amounts of fruit and vegetables [20].

Several studies have found that increasing fruit and vegetable intakes can help to minimize the risk of obesity and CVDs [21–23]. In fact, some studies [24, 25] have identified a negative relationship between low consumption of fruit and vegetables and obesity in Asians, Native Hawaiians/Pacific Islanders and Caucasians. In the USA and Hong Kong, large numbers of firefighters have been found to consume less than the recommended five servings of fruit and vegetables per day [26–28]. It is necessary to explore ways to reduce the risk of obesity and CVDs in firefighters by encouraging them to increase their fruit and vegetable intake. One way of doing so may be to develop an effective strategy for promoting healthy eating.

Healthy eating and physical activity are well-known strategies for reducing the risk of CVDs and promoting health benefits [12, 13, 24, 29]. As explained above, even though firefighters concentrate on physical training, they often overlook healthy eating [6, 7]. Exercise has been found to have only a minimal effect as the first interventional option for managing the weight problems of most overweight or obese people [30]. Furthermore, healthy eating is a modifying factor and can also be a key component to minimize the risk of CVDs. Healthy eating should be promoted, as evidence has shown a positive correlation effect between increased consumption of fruit and vegetables and decreased intake of unhealthy foods in various age groups [31–36].

Several studies have demonstrated the positive effects of health education programmes on healthy eating and the reduction of obesity for various populations [37–41]. Traditionally, information about healthy eating has been delivered through seminars, educational videotapes and pamphlets. However, these delivery methods have limitations, including the long durations of seminars or their restriction to specific venues [13, 42, 43]. It may not be suitable for firefighters to attend lengthy seminars in specific locations, as they work according to unique and special roster patterns that are unpredictable. Therefore, the traditional methods of promoting healthy eating are not always appropriate for firefighters.

Furthermore, there may be a gender factor to be considered. Past studies have demonstrated that males and females have different eating habits. This is due at least partly to differences in body size [44]. Gough and Conner (2006) discovered that females were more aware of healthy eating than were males [17, 45]. Food preferences and eating styles have also been found to be gender-related [46]. Since most firefighters are males [47–49], it is vital to understand more about how to improve the eating habits of male firefighters. Since many firefighters work on either “24 hours on, 48 hours off” or “48 consecutive hours followed by 96 hours off” rotations [50–53], they tend to live and work in their fire stations for 24 or 48 h per shift, eating their meals and spending their leisure time together. Some studies have found that, in general, eating habits are affected strongly by social context [54] and are also influenced by peers, especially away from home [55–57]. Furthermore, it has been found that eating habits are different when people have their meals alone or with peers [54]. In order to minimize any potential bias, the peer influence should be controlled.

The interruptions by unforeseeable calls for emergency care [19], along with the other factors described above, mean that firefighters cannot engage in regular programmes to promote healthy eating. This suggests that flexible delivery methods are needed to facilitate them to join a health promotion programme. Social networking can be a good platform for sharing health-related articles and discussing ideas [58]. Many people consider WhatsApp to be a major messaging service [59]. WhatsApp is a mobile instant messaging application that offers real-time texting or communication [60]. The messages can be retrieved even if the users are offline, out of network coverage or when their devices are switched off when a message is sent, and users can join in the WhatsApp at any time [61]. WhatsApp can be a flexible and effective delivery method for a programme such as health promotion for a group requiring flexible delivery, as firefighters do. The results of several healthy eating promotion programmes delivered through WhatsApp have shown that diverse populations increased their fruit and vegetable consumption, reduced their waist circumferences and decreased their intake of unhealthy snacks [62–65]. Based on the above evidence, WhatsApp has been identified as a social networking platform to promote healthy eating as a way to minimize the risk of obesity and its related adverse outcomes in firefighters.

Several studies have identified the need to identify and implement a theory-based intervention as an effective way to promote behavioral change [66–68]. However, there have been very few theoretically based studies on the promotion of healthy eating habits [66]. The Transtheoretical Model (TTM) has been used to modify risky habits such as smoking, lack of physical activity and unhealthy diets [69–75]. The TTM is an effective theory for motivating changes in eating behaviours in diverse adult populations [25, 76–79]. The TTM consists of a series of five distinct stages of readiness for behavioural change, namely precontemplation, contemplation, preparation, action and maintenance stages [80], based on the cognitive, motivational and behavioural aspects of modifying lifestyle habits [81–83]. This model has been adopted widely to promote healthy eating in different populations [43, 71, 84–88]. One study reported positive results for increasing the intake of fruit and vegetables through applying the TTM to the promotion of healthy eating [89].

The application of TTM has been found to have positive effects on healthy eating and changes to eating habits [43, 87, 90–93]. Additionally, numerous studies have found that baseline stage-matched interventions, matched to the participants’ stages at the baseline (for example, for a participant who is at the precontemplation stage, intervention will also be started at the precontemplation stage), can lead to long-term alterations in the dietary habits of overweight adults [94, 95]. One study recommended that stage matching should be considered when designing education about fruit and vegetable intake [96]. Therefore, a baseline stage-matched intervention could be a worthwhile way to promote healthy eating and encourage participants to change their eating habits [78, 97].

### Research gap

Until now, no other tailor-made health promotion programmes have been found to be effective for male firefighters in Hong Kong, who are precluded from existing programmes due to the nature of their work. There is potential to address this gap by the use of WhatsApp as a vehicle for improving healthy eating habits. Since no previous studies have attempted to do this from a theoretical base, this will be the focus of the current study.

### Study aims

This study has two aims. The first is to determine the feasibility of using a TTM-based printed promotion pamphlet and delivering it with stage-matched teaching materials through WhatsApp to promote healthy eating. The second is to evaluate the potential effects of WhatsApp as a vehicle to promote healthy eating habits in firefighters in Hong Kong. The desired primary outcome is changed eating habits, while the secondary outcomes are body mass index (BMI) and waist-to-hip ratio (WHR).

The following research questions have been set: (1) Will the use of the TTM-based promotion pamphlet and WhatsApp bring about greater changes in their eating habits than the use of the TTM-based pamphlet alone? (2) Will the use of the TTM-based promotion pamphlet and WhatsApp lead to greater changes in the firefighters’ BMIs than the use of the TTM-based pamphlet alone? (3) Will the use of the TTM-based promotion pamphlet and WhatsApp change the firefighters’ WHRs more than the use of the TTM-based pamphlet alone?

In order to address two of the “areas of focus” of a feasibility study (Implementation and Practicality), two more research questions have been posed: If the use of WhatsApp helps to improve firefighters’ eating habits, will this also reduce their BMIs and WHRs and increase their fruit and vegetable intake? Will firefighters find this intervention more useful and efficient than the TTM-based promotion pamphlet?

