### Sample size

There are no clear definitions or guidelines for estimating the sample size for a feasibility study [98]. According to [99], a sample size of 10–15 in a group will probably be sufficient. The proposed sample size was calculated to be 38, allowing for an estimation of the feasibility proportions of adherence and retention to within at least ±17% [100, 101] using a 95% confidence interval with a power of 80% to detect an effect size of 0.6 [77]. The main purposes of this exploratory feasibility study are to collect data to allow the design and sample size calculation for the CRCT.

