### Fidelity of pamphlet

The fidelity of the teaching materials and pamphlet have been established by a panel of experts including three experienced registered nurses, one dietitian and two nutritionists. All of them have more than 10 years of experience in their own areas of expertise. A checklist was completed by each expert. The checklist indicates all components and aspects of the intervention that the participants will receive, from precontemplation to action stages. Self-report measures of consistency will be in binomial (yes/no) and ordinal (1 = Not relevant, 2 = Somewhat relevant, 3 = Quite relevant, 4 = Highly relevant) formats in multiple item surveys. The advantages of using this method are the low cost, ease of administration and speed of data collection. All experts agreed that the proposed teaching materials should include HPI items with stage-based TTM given through WhatsApp. However, one of the experts did not agree with the others on the content of one item. All the items related to goals, processes, strategies and HPI were rated either “Quite relevant” or “Highly relevant”.

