### Data analysis

All of the collected data will be cleaned prior to the analysis process. The data analysis will be conducted by a statistician who is blind to the participants’ group allocation. The participants’ demographic characteristics will be presented using descriptive statistics (mean and standard deviation) for the continuous data, including age, body height and weight plus BMI, and percentage frequencies for the categorical data, including gender, marital status and educational level. Inter-relationships between the variables will be assessed using Pearson’s correlation coefficient. Differences between the intervention and control groups on outcome indicators will be compared using *t* tests and chi-square tests for the continuous and categorical data respectively. The effect of time (baseline; 3 and 6 months after the completion of the programme) on the outcome measurements will be investigated using repeated measures analysis of variance (ANOVA). The impact of “baseline stage matching” on “stage of change” and other outcome measures within the intervention group will be compared using the Kruskal-Wallis *H* test and one-way ANOVA. Normality tests will be conducted. If the data are normally distributed, it will be appropriate to use parametric tests such as one-way ANOVA. But if they are not normally distributed, non-parametric tests such as the Kruskal-Wallis *H* test will be used. *P* values of less than 0.01 will be considered as statistically significant for all comparisons. All statistical analyses will be conducted using SPSS version 22.0. Intention-to-treat analyses will be applied. As of now, there is no clear cut-off for the acceptable proportion of missing data in a dataset for statistical data analysis. Questionnaires with missing rates of more than 10% will be regarded as “disqualified” and excluded from the analysis. Various statistical methods will be used to treat missing data, including replacement by means or values from the regression analyses, depending on the amount and type of missing data.

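### The adherence and retention proportions that help justify n = 38 for the feasibility aim appear in no outcome and no analysis

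*Protocol article*

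**What the plan says.** The protocol article's Study aims section states two aims. The first is feasibility: "The first is to determine the feasibility of using a TTM-based printed promotion pamphlet", delivered together with stage-matched WhatsApp material. The second concerns effect: "The second is to evaluate the potential effects of WhatsApp as a vehicle to promote healthy eating habits in firefighters in Hong Kong".

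On outcomes, the same section says: "The desired primary outcome is changed eating habits, while the secondary outcomes are body mass index (BMI) and waist-to-hip ratio (WHR"). Research questions 1 to 3 ask whether eating habits, BMI and WHR change more in the WhatsApp arm. Two further questions are meant to cover implementation and practicality. One begins "If the use of WhatsApp helps to improve" and goes on to ask about BMI, WHR and fruit and vegetable intake. The other asks whether the men find the intervention more useful and efficient than the pamphlet.

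The Sample size section gives 38, "allowing for an estimation of the feasibility proportions of adherence and retention" to within ±17% with 95% confidence. The same sentence adds 80% power for an effect size of 0.6. The main purpose is to "collect data to allow the design and sample size calculation for the CRCT".

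Under Data analysis, descriptive statistics and Pearson correlations come first. Then: "Differences between the intervention and control groups on outcome indicators will be compared using" t tests and chi-square tests. Repeated-measures ANOVA and Kruskal-Wallis or one-way ANOVA follow, with significance at P<0.01 for all comparisons.

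The section on fidelity says: "The fidelity of the teaching materials and pamphlet have been established by a panel of experts".

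**The concern.** The stated purpose, the basis for the sample size and the specified analysis do not line up. Adherence and retention help to justify the number of participants, but they are not outcomes, no research question asks about them and no analysis estimates them. One of the two questions offered for feasibility is an effect question. Fidelity, as used here, is an expert rating of content made beforehand, and says nothing about whether messages were delivered or read.

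If the plan is followed as written, its main output is a set of between-arm tests that the sample cannot support at the stated power. The planning inputs for the cluster trial would be incomplete: no adherence figure, no interval for retention, and no between-station ICC, because the listed tests work on individuals although fire stations are randomized.

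**Working it through.** **Inputs from the article.** n = 38; target half-width 0.17; 95% confidence; 80% power; effect size 0.6 (Sample size). Significance level 0.01 (Data analysis). Each fire station is a cluster (Participants).

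**Assumptions, because the article does not say.** 38 may be the total or the number per arm, so both are shown. The arms are equal and tests are two-sided. The effect size of 0.6 is read as a standardized mean difference between arms. Adherence is treated as yes or no per man. If it is instead a share of messages per man, its variance cannot exceed 0.25, so the p = 0.5 figures below are upper bounds before clustering.

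**1. The plan's own precision figure.** At p = 0.5, n = 1.96² × 0.25 / 0.17² = 33.2, so 34. With an assumed 10% dropout, 34 / 0.9 = 37.8, so 38. The exact (Clopper-Pearson) interval first reaches a half-width of 0.17 or less at n = 37. The precision half of the justification therefore reproduces.

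**2. Precision that n = 38 gives.** Half-width = 1.96 × √(p(1−p)/n).

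| n | p = 0.5 | p = 0.8 | p = 0.9 |
|---|---|---|---|
| 38 | 15.9 points | 12.7 | 9.5 |
| 19 | 22.5 points | 18.0 | 13.5 |

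The exact half-width at n = 38 and p = 0.5 is 16.6 points. Only the intervention arm receives the WhatsApp material, so if 38 is the total, adherence rests on 19 men and misses ±17 at p = 0.5 and at p = 0.8.

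**3. Clustering.** Design effect = 1 + (m − 1) × ICC, with m men per station. Assuming m = 4 to 8 and ICC = 0.05 to 0.10, the design effect runs from 1 + 3 × 0.05 = 1.15 to 1 + 7 × 0.10 = 1.70. At p = 0.5 the half-widths become 15.9 × √1.15 = 17.0 to 15.9 × √1.70 = 20.7 points for 38 men, and 24.1 to 29.3 points for 19 men.

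**4. The power figure.** Two-sample t test, noncentrality = 0.6 × √(n per arm / 2), before any design effect.

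| Reading of 38 | Noncentrality | Power at 0.05 | Power at 0.01 |
|---|---|---|---|
| Total (19 per arm) | 1.85 | 44% | 21% |
| Per arm | 2.62 | 73% | 49% |

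For 80% power the t test needs 45 per arm at 0.05 and 67 per arm at 0.01. A paired comparison would need 24 men at 0.05 and 36 at 0.01, but research questions 1 to 3 compare arms.

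**5. How well the ICC could be estimated.** Approximate SE = (1 − ICC) × (1 + (m − 1) × ICC) × √(2 / (m(m − 1)(k − 1))), with k = 38/m stations. For m = 4, k = 9.5 and ICC = 0.05: 0.95 × 1.15 × √(2 / (12 × 8.5)) = 0.15. Over m = 4 to 8 and ICC = 0.05 to 0.10 the SE is about 0.13 to 0.16, larger than the ICC itself.

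**6. Where each quantity appears.**

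| Quantity | Sample size | Outcomes or research questions | Data analysis |
|---|---|---|---|
| Adherence | yes | no | no |
| Retention | yes | no | no |
| Eating habits, BMI, WHR | covered by the effect size statement | yes | yes, as outcome measures |
| Usefulness | no | yes | not named |
| Station ICC | implied by the stated purpose | no | no |

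**The case against.** A reader might infer that the trial cannot answer its first aim at all, that the analysis consists only of efficacy tests, or that a non-significant result would be taken to mean not feasible. The documents do not support this.

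- The second aim is about potential effects, and the outcomes, research questions 1 to 3 and between-arm comparisons serve it. The sizing sentence also claims power for an effect, so effect testing does not contradict the stated sizing basis.
- Data analysis includes means, standard deviations and correlations. The SD of BMI would be available at least at baseline, and SDs come with routine t-test output.
- Usefulness is partly covered. The questionnaire has three 4-point items on healthy eating programmes, pamphlets and mobile-app delivery. They are worded generally and are not named as an outcome.
- Retention can be counted from attendance at T0, T1 and T2, and adherence to sent messages would normally be logged by the sender rather than asked in a questionnaire.
- Nothing in the article ties a feasibility conclusion to a P value.

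It can also be said that a condensed article leaves definitions, logs and interval methods to the full protocol or SAP. That holds for the detail. It does not cover the core, because the article itself fixes the outcomes, the research questions and the tests, and the quantities it used to justify 38 are in none of them.

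**Conclusion.** The point holds in limited form. Feasibility is the first aim, and the precision of adherence and retention is part of the reason for 38, yet neither is named as an outcome or given an analysis. The effect analyses are legitimate for the second aim but are not adequately powered. Before clustering, no reading of 38 gives 80% for a two-arm difference of 0.6: power ranges from 21% to 73%, depending on the significance level and on whether 38 is the total or per arm. What 38 supports is estimation, to ±15.9 points at p = 0.5 over all participants if 38 is the total. Intervention-arm adherence is then known only to ±22.5 points. If 38 is per arm, adherence is known to ±15.9 points. Clustering widens all of these by an amount that depends on station size and ICC, neither of which the article gives.

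**What to change.** In Study aims and Data analysis, name two feasibility outcomes that answer the first aim: retention at T2, by arm, and adherence in the intervention arm, defined as the share of two-weekly WhatsApp deliveries received or read, taken from message records. Give each a 95% CI that allows for station.

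Report eating habits, BMI and WHR as exploratory between-arm differences with 95% CI and SD, allowing for station, and draw no efficacy conclusion from P values. Report the station ICC with its CI, and say that with few stations it will be too imprecise to size the next trial alone. State whether 38 is the total or per arm.

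The cost is some rewording and a station-level term in the models. The claim to test efficacy is given up. The Trial status section gives a completion date of 29 February 2020, so this would now be a re-specified analysis and should be dated and labelled as such. Retention, effect estimates and the ICC can still be obtained from the collected data, but adherence can be reported only if message records were kept.
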